### **Type of research**

Quadruple-Blind Randomized, Monocentric, Placebo-controlled Study. No profit.

[figure not shown]

## University of Naples “Federico II” - Naples, Italy

### **Background**

Childhood obesity has emerged as an important global health concern that is associated with emergence of comorbidities previously considered to be “adult” diseases including type 2 diabetes mellitus, hypertension, nonalcoholic fatty liver disease, obstructive sleep apnea, and dyslipidemia (1).

According to the World epidemiological data of WHO 38 million children under 5 years were overweight or obese in 2019 and over 340 million children and adolescents aged 5-19 were overweight or obese in 2016 (2).

Obesity arises from complex interactions between genes and environmental factors such as diet, food components and/or way of life, and results from a long-term positive imbalance between energy intake and expenditure with excessive increase in body fat (3).

It is now well established that gut microbiota (GM) can influence human health and a growing body of evidence suggests that GM play a metabolic role in energy regulation and substrate metabolism (4). Various factors can impact GM and several underlying mechanisms have been proposed, one of these are fermentable dietary fibers that represent the fraction of not digested food by endogenous enzymes in the small intestine which are converted into an array of small organic metabolites by microbes in the large intestine, the most important are short-chain fatty acids (SCFA)

[figure not shown]

## University of Naples “Federico II” - Naples, Italy

acetate, propionate and butyrate (5, 6). Of the SCFAs, in particular butyrate supplementation was found to have multiple metabolic benefits in murine models, including prevention of high-fat diet (HFD) induced obesity, insulin resistance (IR) and hepatic steatosis (7, 8, 9,10).

With the dramatically increase of obesity prevalence seen in the pediatric population, novel insights are necessary to counteract this epidemic disease, so a reasonable speculation is that butyrate acts on components of the energy balance, that is, stimulating energy expenditure, and/or reducing energy intake, thereby reducing obesity and obesity-associated disorders.

*Li et al* (11) report that acute oral butyrate administration decreased food intake in HFD fed mice, suppressed the activity of orexigenic NPY neuron activity in the hypothalamus indicating the effect of butyrate on satiety; in addition to inducing satiety, butyrate also promoted fat oxidation and activated brown adipose tissue, evident from increased utilization of plasma triglyceride-derived fatty acids.

Alternatively, the metabolic benefits of butyrate may be induced by satiety gut hormone Peptide YY (12) or by stimulation of GLP-1 secretion from L cells of the gastrointestinal (GI) tract, which activates GLP-1 receptor signalling in the vagal nerve and consequently induces hypothalamic satiety signaling (13, 14).

[figure not shown]

## University of Naples “Federico II” - Naples, Italy

In this context oral butyrate administration in obese children could induce body weight loss, that can be achieved by decreasing energy intake, reducing the consumption or absorption of food, and/or by increasing energy expenditure.

The aim of this study is to evaluate the effects of 6-month oral butyrate supplementation compared to placebo in a cohort of obese pediatric patients in addition to standard care for pediatric obesity treatment.

## **Aims**

### **Main study outcome**

- To determine the effectiveness on child weight status (BMI z-score reduction)

### **Secondary study outcomes**

- To evaluate glucose metabolism parameters (glycemia, insulinemia, HOMA Index), lipid metabolism parameters (total cholesterol, LDL, HDL and triglycerides), serum levels of the hormone ghrelin and of the proinflammatory cytokine IL-6, and on the expression of microRNA-221;
- To assess dietary and lifestyle habits;
- To assess metagenomic characteristic of the gut microbiota.

[figure not shown]

## University of Naples “Federico II” - Naples, Italy

### *Population*

#### **Inclusion criteria**

Children/adolescents with diagnosis of obesity (BMI >95° percentile for age and sex), 5-17 years, observed at Pediatric Section of Department of Translational Medical Sciences (University of Naples Federico II).

#### **Exclusion criteria**

- Age at enrollment <5 or >17 years
- BMI <95° percentile for age and sex
- Patients under pharmacological treatment for obesity (metformin)
- Patients assuming vitamin E,
- Patients assuming pre-, pro- or synbiotics
- Simultaneous presence of other chronic diseases unrelated to obesity: cancer, immunodeficiency, cystic fibrosis, allergies, celiac disease, autoimmune diseases, neuropsychiatric disorders, type 1 diabetes, inflammatory bowel diseases, malformations of urinary or gastrointestinal or respiratory tract, chronic lung diseases, genetic and metabolic diseases, chronic hematological diseases.
- History of surgery for the treatment of obesity
- Any medical condition that may interfere with participation in this study
- Participation in other clinical trials still in progress

[figure not shown]

## University of Naples “Federico II” - Naples, Italy

### *Study Design*

Quadruple-Blind Randomized, Monocentric, Placebo-controlled Study.

Obese patients related to the Pediatric Section of Department of Traslational Medical Science of the University of Naples "Federico II" will be evaluated for the study.

At the baseline, inclusion and exclusion criteria will be assessed and the aims and methods of the study will be illustrated to parents/tutors and young patients. After obtaining informed consent from the patients and their parents/tutor (Annex 1.), patients will be enrolled and randomly assigned to two group of 6-month intervention.

Group 1: standard care for pediatric obesity + sodium butyrate (20 mg/kg body weight/day)

Group 2: standard care for pediatric obesity + placebo (cornstarch)

The packaging, color, weight, smell and taste of the active product and of the placebo will be identical without indication of group identity or content and will be labeled with a serial number according to the computer-generated randomization list, and thus ensured blind conditions.

Instructions for keeping and maintaining the product will be also providing.

All study subjects will be evaluated by a multidisciplinary team (composed by pediatricians, nutritionists and pediatric nurses experienced in the care of pediatric obesity).

Anamnestic, demographic, anthropometric and clinical data will be

[figure not shown]

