## University of Naples “Federico II” - Naples, Italy

### **Sample size**

Considering a possible drop-out of 10%, will be required 27 patients per group (Group 1: n=27; Group 2: n=27) to observe a BMI z-score reduction at least of  $\geq 0.25$  after 6 months of intervention (Power of the study 90%; type 1 error =0.050, 2- tailed test).

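### Ages 5 to 17 at 27 per arm: no age stratum is named, arms are compared unadjusted and pubertal stage is not recorded, so precision is lost and a chance imbalance in puberty could be neither seen nor adjusted for, mainly for insulin, HOMA-IR and ghrelin

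*Protocol*

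**What the plan says.** - **Population** (Protocol, Inclusion criteria): "Children/adolescents with diagnosis of obesity (BMI >95° percentile for age and sex), 5-17 years".
- **Allocation** (Study Design): "patients will be enrolled and randomly assigned to two group of 6-month intervention". Active product and placebo "will be labeled with a serial number according to the computer-generated randomization list". No stratum, block size or minimisation factor is mentioned.
- **Size** (Sample size): "Considering a possible drop-out of 10%, will be required 27 patients per group (Group 1: n=27; Group 2: n=27"), for a BMI z-score reduction of 0.25, with "Power of the study 90%; type 1 error =0.050, 2- tailed test". No standard deviation is given.
- **Outcomes**: the main one is "To determine the effectiveness on child weight status (BMI z-score reduction"). The secondary list begins "To evaluate glucose metabolism parameters (glycemia, insulinemia, HOMA Index") and goes on to lipids, ghrelin, IL-6 and microRNA-221.
- **Analysis** (Statistical analysis): arms are compared by a test of means or the Mann-Whitney test, with Welch's t test also named. The regression for outcomes lists dietary, anthropometric, glucose and lipid variables. Demographic data enter only the model for microbiota composition.
- **Data collected** (Study Design visit list and Annex 2): weight, height, BMI, percentiles, waist, blood pressure, food record, laboratory values and stool sample. Birth date is in the Annex 2 header. Pubertal stage appears in neither place.
- **Visits** (Compliance and safety monitoring): a full clinical evaluation takes place at each monthly visit.

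**The concern.** A 5-to-17 cohort runs from prepubertal to near-adult children. It is reasonable to expect that the six-month course of fasting insulin, HOMA-IR and ghrelin depends on age and puberty, and that the BMI z-score response to standard care does so to a lesser degree. With 27 per arm and no stratum named, chance can leave one arm noticeably younger or less advanced in puberty.

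Two things are at stake. First, any outcome spread explained by age stays in the error term of an unadjusted comparison. Second, if an imbalance in pubertal stage occurs, nobody can detect it or correct for it, because the variable is not on the chart. A statistical analysis plan can add an age covariate later, but it cannot recover an enrolment stage that was never recorded.

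**Working it through.** **1. The plan's own figure.** Inputs from Sample size: difference 0.25, power 90%, two-sided alpha 0.05, drop-out 10%. No SD is stated, so 27 cannot be reproduced directly, and the SD has to be back-solved from 24 evaluable per arm (24 / 0.9 = 26.7, rounded up to 27).

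- Formula: n = 2(1.960 + 1.282)² SD² / 0.25².
- For n = 24: SD = 0.25 / (3.242 × √(2/24)) = 0.267. With the t distribution, SD = 0.262.
- Check: 2 × 10.51 × 0.267² / 0.0625 = 24.0.

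This reads the 0.25 as a difference between arms, which the section does not say.

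**2. Chance imbalance in age.** Assumption: 40-50% of children are under 11. The number of younger children in each arm is taken as Binomial(27, p).

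| Gap between arms | p = 0.4 | p = 0.5 |
|---|---|---|
| 5 or more children (19 points) | 0.211 | 0.220 |
| 6 or more children (22 points) | 0.126 | 0.134 |

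Both directions are counted. If the total of younger children is held fixed instead (22 or 27 of 54), the probability of a gap of six or more is 0.17 or 0.10. The order of magnitude therefore does not depend on the sampling model.

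For mean age, SE = SD × √(2/27). With an assumed age SD of 3.0-3.75 years, SE is 0.82-1.02 years. A gap above one year then has probability 22-33%, and a gap above two years 1-5%.

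**3. Consequence for BMI z-score.** Assumption: younger children change by d = 0.1, 0.2 or 0.3 more than older ones. A six-child gap moves the arm difference by d × 6/27.

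| d | Shift | Share of 0.25 | Variance explained, 0.25d²/0.262² (equal split) |
|---|---|---|---|
| 0.1 | 0.022 | 9% | 3.6% |
| 0.2 | 0.044 | 18% | 14.6% |
| 0.3 | 0.067 | 27% | 32.8% |

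These shifts are conditional on an event of about 13% probability. The typical (one SD) shift at p = 0.5 is d × √(0.5/27) = d × 0.136, or 0.014-0.041. The standard error of the treatment difference is 0.262 × √(2/24) = 0.076, and it already includes this component.

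**4. Type I error.** The simulation used 24 per arm, half of the children pubertal, SD 0.267 and an unadjusted t test. Overall error stays at about 5% whatever the pubertal gap in BMI z change. Given an imbalance of 20 points or more, it is about 6% for a gap of 0.1 and about 9% for 0.2.

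**5. Gain from adjustment.** If covariates explain a share R² of the variance, the SD becomes 0.267 × √(1 − R²). With 24 per arm, power goes from 90% to 91.4% (R² = 0.05), 92.8% (0.10) and 95.2% (0.20).

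**6. Insulin, HOMA-IR and ghrelin.** The document gives no variance or target difference for these outcomes, so no size can be computed. The point for them is structural: they are not described as age-standardised, and pubertal stage is not collected.

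**The case against.** The strongest reply is that this is a randomised, blinded comparison with a placebo arm followed over the same six months. Growth and puberty affect both arms and are balanced in expectation. This stands. A reader might infer that growth and puberty cannot be separated from a butyrate effect; that would apply to a single-arm study, and the documents do not support it here. Overall type I error is preserved, and the standard error already carries the ordinary chance imbalance.

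Several further replies also stand:

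- BMI z-score is standardised for age and sex, which removes much of the age effect from the main outcome.
- Age can be derived from birth date, and height is measured monthly, so age and growth can be adjusted for. Only pubertal stage cannot be recovered.
- The construction of the list is undescribed; the protocol does not say that it is unstratified.
- The share under 11 and the 0.1-0.3 gap are assumptions, and the top of that range exceeds the 0.25 treatment target.
- Nothing in the protocol is contradicted, and stratification in a 54-patient single-centre trial is optional.

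It might also be said that covariates belong in a statistical analysis plan that is not shown. That holds only in part: the protocol itself specifies unadjusted tests for the arm comparison, and the content of the chart is settled before the first child enters.

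**Conclusion.** The point holds as a cheap improvement; it is not a flaw that invalidates the trial. The protocol names no age stratum, compares arms unadjusted and does not record pubertal stage in a 5-to-17 cohort of 27 per arm. The cost is some precision, plus a chance imbalance in puberty that could be neither seen nor adjusted for. This weighs most on insulin, HOMA-IR and ghrelin, where its size cannot be stated from the document.

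For BMI z-score the effect is smaller: a typical shift of 0.014-0.041, or 0.02-0.07 given a six-child gap with a chance of about 13%. Both ranges depend on the assumed age split and the assumed 0.1-0.3 gap. Adjustment would raise power from 90% to about 91-95% for R² of 0.05-0.20.

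A reader might also infer that the sample size leaves no slack. The document gives no SD, so that cannot be judged, and it forms no part of this point.

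**What to change.** 1. **Study Design**: generate the list in permuted blocks within two age bands, for example 5-10 and 11-17 years, and say so.
2. **Statistical analysis**: compare the arms on the primary outcome and on insulin, HOMA-IR and ghrelin with a model that includes age or the age stratum.
3. **Annex 2**: add a pubertal-stage row at Enrollment and V6, completed at the clinical evaluation already scheduled. Use the T0 stage as a covariate for insulin, HOMA-IR and ghrelin. This row must be in place before enrolment begins.

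The cost is slightly more complex kit numbering, one chart row, and one or two model degrees of freedom. No visit is added.

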## University of Naples “Federico II” - Naples, Italy

collected and reported in a specific clinical chart ([Annex 2.](#)).

The patients and their parents/tutor will be instructed on how to complete a food record ([Annex 3.](#)) for the evaluation of dietary patterns which will subsequently be analyzed by a specific software (Winfood - Medimatica Srl). Compliance with the recommendation regarding physical activity and sedentary behaviors at T6 was assessed by questioning about lifestyle habits ([Annex 4.](#)).

At enrollment (T0) and every month for 6 months (T1, T2, T3, T4, T5, T6) will be evaluated: body weight, height, BMI, weight for age percentile, height for age percentile, BMI for age percentile, waist circumference, blood pressure, eating behavior (3 days food record).

At the baseline (T0) and at the end of the study (T6) peripheral blood sampling will be performed for the evaluation of fasting blood glucose, basal insulin, HOMA-IR index, triglyceride, HDL cholesterol, LDL cholesterol, total cholesterol, ghrelin, and expression profile from PBMCs of miR-221. At enrollment (T0), before the start of interventions, and after 6 months (T6) a stool sample for each patient (3 g) will be collected for the metagenomic analyses of the gut microbiota. All samples will be collected from diapers in sterile plastic tubes and stored at -80°C until analysis.

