### *Compliance and safety monitoring*

At each visit, the compliance to the allocated treatment will be assessed based on number of capsules unit left in the box. Compliance to the allocated treatment was defined as the consumption of 100% of the capsules. Furthermore, compliance with the recommendation regarding physical activity will be assessed by questions about daily exercises.

A dedicated phone number was available 7 days per week for parents/legal guardians of each patient in the case of occurrence of any suspected adverse event and at each monthly visit the safety will be monitored through a full clinical evaluation. Unscheduled visits will be performed if necessary.

[figure not shown]

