# University of Naples “Federico II” - Naples, Italy

## Annex 4.

### Questionnaires regarding physical activity and sedentary behaviors.

|                                                                                                                                    |                                         |                                          |                                       |                                       |                                               |                                                                               |                                    |                                    |                                                                                |
|------------------------------------------------------------------------------------------------------------------------------------|-----------------------------------------|------------------------------------------|---------------------------------------|---------------------------------------|-----------------------------------------------|-------------------------------------------------------------------------------|------------------------------------|------------------------------------|--------------------------------------------------------------------------------|
| On how many days in the past week were you physically active for 60 minutes or more?                                               | 0 days
      | 1 days
       | 2 days
    | 3 days
    | 4 days
            | 5 days
                                            | 6 days
 | 7 days
 |  <
or
 ≥ 5
times/week |
| Outside school hours, how many hours a week do you usually exercise in your free time so much that you get out of breath or sweat? | 30 minutes
  | 1 hour
       | 2-3 hours
 | 4-6 hours
 | ≥7 hours
          |  <
or
 ≥ 2
hour/week |                                    |                                    |                                                                                |

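### The only instrument for exercise and screen time, part of a secondary outcome, is scheduled at T6 alone, so change in these habits cannot be described or baseline-adjusted

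*Protocol*

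**What the plan says.** Under Secondary study outcomes, the protocol includes the aim "To assess dietary and lifestyle habits". It gives no measure or time point there.

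The Study Design section supplies the schedule:

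- **Diet** is covered at T0 and every month. The list of repeated measurements ends with "waist circumference, blood pressure, eating behavior (3 days food record", and the Annex 2 chart has a food-record row from enrolment to V6.
- **Exercise and screen time** are covered by Annex 4, titled "Questionnaires regarding physical activity and sedentary behaviors". The section assigns it to one visit: "Compliance with the recommendation regarding physical activity and sedentary behaviors at T6 was assessed by questioning about lifestyle habits".
- **The items collected at both T0 and T6** are blood and stool samples.

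The Compliance and safety monitoring section opens with "At each visit, the compliance to the allocated treatment will be assessed based on number of capsules unit left in the box". After defining treatment compliance it adds that "compliance with the recommendation regarding physical activity will be assessed by questions about daily exercises". That clause names no visit, does not cite Annex 4 and leaves out sedentary behaviour.

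The Annex 2 chart has columns from enrolment to V6 but no activity or sedentary row. Annex 4 as shown has no field for the visit.

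**The concern.** Half of this secondary outcome has a baseline and monthly follow-up. The other half has a single reading after six months of intervention. Both arms receive standard obesity care, and the protocol itself refers to a recommendation on activity and sedentary time. A reader will therefore want to know whether children became more active or cut their screen time, and whether the arms were alike on this at entry. With T6 alone, neither question can be answered.

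This is not a detail that a statistical analysis plan could settle later. When an instrument is given is fixed by the protocol, and a T0 answer that was never collected cannot be recovered by analysis. A lifestyle value measured only at T6 is also post-randomisation, so it is unsuitable as an adjustment covariate for the BMI z-score effect.

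**Working it through.** The plan states no figure on this point. The check is first a reading of the schedule, then an illustration of size.

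**Step 1. Where is a lifestyle value scheduled?**

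| Place in the protocol | Diet | Exercise and screen time |
|---|---|---|
| Study Design, T0 and monthly list | Yes | No |
| Study Design, T0 and T6 samples | Not applicable | No |
| Study Design, Annex 4 sentence | Not applicable | T6 only |
| Compliance and safety monitoring | Not mentioned | Exercise questions, timing not stated |
| Annex 2 chart | Row, enrolment to V6 | No row |
| Annex 4 | Not applicable | Five items, no visit field |

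No entry gives a T0 value for exercise or screen time. The compliance sentence does not fill the gap on either reading of its timing: it concerns adherence to a recommendation, which has no meaning before the advice is given.

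**Step 2. How different could the arms be at entry by chance?** Annex 4 sorts its items against two-category cut-offs, so take a yes/no item. Inputs: 27 per arm (Sample size section) and 50% prevalence (my assumption).

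- SD of the difference in proportions = √(2 × 0.25 / 27) = 0.136, or 13.6 percentage points.
- Probability of a gap of 6 or more children out of 27 (6/27 = 22 points), exact binomial = 0.134.

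So about 13% of randomisations would produce a gap of that size on a given item, and the trial could not see it.

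**Step 3. How precise is the T6 comparison?** The sample size statement is "Considering a possible drop-out of 10%, will be required 27 patients per group". Allowing for 10% loss, 27 × 0.9 = 24.3, so about 24 per arm are evaluable.

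- 95% half-width for an unadjusted difference = 1.96 × √(2 × 0.25 / 24) = 0.283, or about 28 points.

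**Step 4. What would a T0 value add?** In a linear model the standard error is multiplied by √(1 − r²), where r is the T0–T6 correlation. The documents give no r, so I show a range.

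| Assumed r | SE multiplier | Reduction in SE | Half-width (28.3 × multiplier) |
|---|---|---|---|
| 0.5 | √0.75 = 0.87 | 13% | about 25 points |
| 0.7 | √0.51 = 0.71 | 29% | about 20 points |

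For a yes/no item this multiplier is only an approximation, for a risk difference with linear adjustment. For a continuous score with 24 per arm, two-sided 0.05 and 80% power, the detectable standardised difference is (1.96 + 0.84) × √(2/24) = 0.81 with T6 only. It falls to 0.70 at r = 0.5 and 0.58 at r = 0.7.

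**The case against.** The strongest defence is that the aim is to assess habits, not to measure change. Annex 4 is introduced as a check on compliance with advice, and its cut-offs suit one end-of-study reading. A randomised comparison at T6 needs no baseline to be unbiased. All of this stands, and it limits the point to description and precision.

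Three stronger readings are tempting, but the protocol does not support them:

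- **That two sections contradict each other on timing.** A reader might take the compliance paragraph to schedule the Annex 4 activity questions at every visit. Its reference to each visit governs the capsule count. The exercise sentence names no visit and does not cite Annex 4, so it may describe a separate, informal question. The timing is unclear, but a clash is not shown.
- **That the primary result is compromised.** Randomisation and blinding protect the BMI z-score comparison, and chance imbalance in activity is already allowed for in the type 1 error. A change in habits caused by the treatment would be part of its effect, not confounding. The Statistical analysis section names dietary, anthropometric, glucose and lipid variables as influences to examine; it does not name activity.
- **That the whole secondary outcome lacks a baseline.** Diet has one.

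It is also fair to say that the wide interval at T6 comes mainly from the sample size. Even at r = 0.7 it remains about 20 points either side.

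**Conclusion.** The gap is real and of moderate weight. A named secondary outcome includes exercise and screen time, yet their only instrument is given once, at the end. The trial can compare arms at T6 without bias. It cannot describe within-child change, show how the arms compared at entry, or gain precision from a baseline value. The omission at T0 follows directly from the text and rests on no assumption.

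The size is illustrative: a standard error about 13% to 29% lower if the T0–T6 correlation is 0.5 to 0.7. The correlation and the 50% prevalence are assumptions, and the linear-model formula is approximate for yes/no items. Neither the validity of the T6 comparison nor the BMI z-score result is in question.

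**What to change.** 1. In Study Design, schedule Annex 4 at T0, before the first dose, and at T6.
2. Add a matching row to the Annex 2 chart, and a visit field to Annex 4 so that the two forms can be told apart.
3. In Compliance and safety monitoring, state whether the daily-exercise questions are those of Annex 4, and at which visits they are asked.
4. Compare arms at T6 adjusted for the T0 answer. If lifestyle is used as a covariate for BMI z-score, use only the T0 value. The analysis plan can carry this item, but items 1 to 3 belong in the protocol.

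The cost is five short questions at a visit that already takes place, a few minutes per child, and small edits to the text and forms. The change must be made before a child's first dose, because a missed T0 answer cannot be obtained afterwards.

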### **Statistical analysis**

The Kolmogorov-Smirnov test will be used to determine whether variables will be normally distributed. For continuous variables the study groups will be compared using the mean equality test or, if necessary, the Mann-Whitney U test. The Kruskal-Wallis H-test will be used to compare the two groups. The comparison between two groups and between two samples will be performed using Welch's t test and Fisher's exact test respectively (with Bonferroni's correction). The  $\chi^2$  test and Fisher's exact test will be used for categorical variables. The data obtained will be assessed by means of linear logistic regression analysis in order to evaluate the possible influence of dietary factors and other variables (anthropometric data, glucose and lipid metabolism variables). We will use a generalized linear regression model (GLM) to examine the contribution of demographic, anamnestic and clinical data of children enrolled on the composition of the microbiota. A GLM model will be built and validated using the rms and ResourceSelection packages implemented in R respectively (<http://www.r-project.org/>). Multivariate statistical analysis (Analysis of the Main

[figure not shown]

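### The protocol's unadjusted two-sample tests neither combine the six monthly on-treatment diet records nor use the baseline record (minor; secondary outcome)

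*Protocol*

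**What the plan says.** The secondary outcomes in the Protocol include "To assess dietary and lifestyle habits", with no diet variable, summary or time point.

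The visit schedule in Study Design reads "At enrollment (T0) and every month for 6 months (T1, T2, T3, T4, T5, T6) will be evaluated", and the list that follows includes "waist circumference, blood pressure, eating behavior (3 days food record"). The Annex 2 chart has a food-record box at enrolment and at all six visits. That makes seven records per child, six of them on treatment (6 x 3 = 18 days). The records are kept "for the evaluation of dietary patterns which will subsequently be analyzed by a specific software"; no rule for combining visits is given.

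The Statistical analysis section says: "For continuous variables the study groups will be compared using the mean equality test", with Mann-Whitney as the alternative. It also lists Kruskal-Wallis, Welch's t test, chi-square and Fisher's exact test. All take one value per child. Of the models named, one uses dietary factors as explanatory variables and the other has microbiota composition as its response. No repeated-measures or baseline-adjusted comparison of the arms appears.

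The Background explains possible weight loss as something "that can be achieved by decreasing energy intake, reducing the consumption or absorption of food, and/or by increasing energy expenditure".

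**The concern.** The protocol sets an intensive diet schedule and lists its tests one by one, but the two do not fit together. The tests accept one number per child, and the protocol does not say which number. The T0 record has no role in the comparison of arms.

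A 3-day record carries both stable differences between children and day-to-day variation. Averaging over visits reduces the second. Adjusting for T0 removes part of the first. An unadjusted test at one visit does neither.

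What is at stake is how far the diet result can be interpreted. Lower intake is one of the routes by which the protocol expects butyrate to work. With about 24 evaluable children per arm, an imprecise comparison could miss a real difference, and a null result would say little. Leaving the visit and summary open also allows a choice among six visits after the data are seen.

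**Working it through.** **Inputs from the Protocol.** 27 per group with 10% drop-out: 27 x 0.9 = 24.3, taken as 24 per arm. Alpha 0.05, two-sided. Three days per record, one record at T0 and six from T1 to T6.

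**Assumed inputs.** The documents give none of these: between-child CV (B) 15, 20 or 25%; within-child daily CV (W) 20, 25, 30 or 35%; a 15% difference in mean intake, constant from T1 to T6. This makes 12 combinations. The central case is B = 20%, W = 25%.

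**The plan's own figure.** There is none for diet. The 27 per group refers to BMI z-score, with no SD stated, and is used here only for the number of children.

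**Formulas (variance per child).**
- One record: V1 = B² + W²/3
- Mean of six records: V6 = B² + W²/18
- T6-T0 change: 2W²/3
- Adjustment for T0 subtracts B⁴/(B² + W²/3) from V1 or V6

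Power is that of a two-sample t test, 24 per arm.

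**Central case.**
- V1 = 0.0400 + 0.0625/3 = 0.0608
- V6 = 0.0400 + 0.0625/18 = 0.0435
- Change: 2 x 0.0625/3 = 0.0417
- T0 adjustment: 0.0016/0.0608 = 0.0263
- Adjusted single record: 0.0608 - 0.0263 = 0.0345
- Adjusted mean: 0.0435 - 0.0263 = 0.0172

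| Analysis | Variance | Power, central case | Power, 12 combinations |
|---|---|---|---|
| One record, unadjusted | 0.0608 | 54% | 35-77% |
| Six-record mean, unadjusted | 0.0435 | 68% | 49-90% |
| T6-T0 change | 0.0417 | 70% | 43-88% |
| One record, adjusted for T0 | 0.0345 | 78% | 51-93% |
| Six-record mean, adjusted for T0 | 0.0172 | 97% | 82% to over 99% |

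The adjusted mean has the highest power in all 12 combinations.

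**Separating the two gains.** From one unadjusted record, averaging alone moves central power from 54% to 68%, and T0 adjustment alone from 54% to 78%. Both together give 97%. Averaging alone is worth V1/V6 = 1.2 to 2.2 times the sample size over the range.

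**Visit-by-visit testing.** If all six visits were tested at 0.05/6, the chance of at least one significant visit in the central case is about 57% (simulation, 20,000 trials). That is close to a single record.

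**Sensitivity.** If a child's true intake also varies between visits with an SD of 10-15%, the adjusted mean falls from 97% to 92-86%. One unadjusted record falls from 54% to 48-42%.

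**Cross-check.** Put instead as a correlation of 0.2 to 0.8 between a child's monthly records, the variance of the six-record mean relative to one record is (1 + 5 x correlation)/6, or 0.33 to 0.83. That equals 3.0 to 1.2 times the sample size, the same direction and similar size.

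**The case against.** A reader might infer that a single 3-day record will decide whether butyrate lowered energy intake. The documents do not support that. No visit is named for diet. A two-sample test can be run on a T1-T6 mean or on a change from T0, so the named tests do not rule out averaging. Nor is energy intake a stated endpoint: it appears in the Background as one possible mechanism, beside absorption and expenditure, while the outcome is worded as dietary and lifestyle habits.

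It can also be said that summarising visits for a secondary outcome belongs in a statistical analysis plan, which is not shown and may settle it. This holds for the missing summary rule taken alone, and it keeps the severity low. It does not remove the point, because the protocol does list its group comparisons and every one is unadjusted.

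A further objection is that the gain should not all be credited to averaging out measurement noise. That is correct: much of it comes from T0 adjustment. The simple T6-T0 change, which the named tests permit, gives 70% in the central case, slightly above the unadjusted six-record mean. The adjusted mean still does better than every alternative checked.

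Finally, the CVs and the 15% difference are assumptions. The direction does not hang on one choice of them, but the size does.

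**Conclusion.** The point holds as a minor improvement. The listed comparisons neither combine the six on-treatment diet records nor use the T0 record, though all seven are scheduled. Using both raises power in the central case from 54% (one unadjusted record) or 70% (T6-T0 change) to 97%. Across the assumed CVs the ranges are 35-77%, 43-88% and 82% to over 99%.

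These figures rest on 24 children per arm with complete records, an assumed 15% difference constant over T1-T6, and a stable between-child component. They are somewhat lower if true intake varies between visits. The primary BMI z-score comparison is not affected.

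**What to change.** Name one diet variable, for example mean daily energy intake, which matches the protocol's own proposed mechanism. Compare arms on each child's mean over the available T1-T6 records, in a linear model with the T0 value as covariate. Treat single visits and other nutrients as descriptive.

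The cost is a sentence or two in the Statistical analysis section or the analysis plan, with no new visits or records. The downside is that the mean describes the whole treatment period, not month 6 alone, so an effect that appears only late would be diluted. The T6 value can be shown beside it descriptively.
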